### Measures

Primary and secondary exposure and outcome measures are included in Table 1. Primary exposure for the intent-to-treat analysis is classified as the clinic randomization arm: SMS intervention, PN intervention, and SOC. The primary study outcome is retention in care, which is defined for patients on ART as the proportion of patients who have initiated ART who remain on treatment at 6 and 12 months and for patients who are not yet eligible as the proportion of patients who undergo a repeat CD4 test at 6 months and 12 months after the initial CD4. The secondary outcome of linkage to care is defined as a patient undergoing CD4 staging or being assessed for ART eligibility within 3 months of a positive diagnosis. We will also monitor whether the participants are linked to ART – that is, whether eligible participants receive ART within 3 months of CD4 staging. The secondary outcome of adherence is being assessed in three ways: as a report of taking 90 % of the prescribed medication, as no report or clinical record indicating gaps in treatment of 4 or more days, and collection of the proportion of days covered by medication dispensed. Finally, prevention behavior is defined as the number of unprotected sex acts by HIV partner status. All outcomes will be measured using both clinical record extraction and self-report; these two means of data collection will be compared for accuracy (using clinical record extraction as the gold standard).

**Table 1 Tab1:** Measures, data sources, and data collection schedules for protocol exposures and outcomes

Domain	Instrument/measure	Data source	Data collection schedule
PRIMARY EXPOSURE			
Clinic randomization assignment	Clinic where participant receives care	Intake form	Baseline
SECONDARY EXPOSURE			
Intervention Dosage	Minutes of intervention received	PN participant contact forms and CommConnect system records	Ongoing capture
PRIMARY OUTCOMES			
Retention in HIV care	Patients on or initiating ART who remain on treatment 6 and 12 months later (with documented receipt of treatment)	Intake and Record extraction	Weekly (ART)
		Survey data (self-report)	0, 6, and 12 months
	Patients not ART eligible who have a repeat CD4 test at 6 months and 12 months after initial CD4	Intake and Record extraction	Bi-weekly (pre-ART)
		Survey data (self-report)	0, 6, and 12 months
SECONDARY OUTCOMES			
Linkage to HIV care	CD4 drawn and results available at clinic within 3 months of testing HIV positive	Intake and Record extraction	Weekly (ART) bi-weekly (pre-ART)
	CD4 result received within 3 months of testing HIV positive	Survey data (self-report)	0 and 6 months
	Patients eligible for ART who initiate treatment within 3 months of CD4 staging	Intake and Record extraction	Weekly (ART)
		Survey data (self-report)	0, 6, and 12 months
Adherence to ART	Proportion taking 90 % and 100 % of pills in the past 30 days	Survey data (self-report)	0, 6, and 12 months
	Breaks in treatment during the previous six months (at least 4 days in a row)	Intake and Record extraction	Weekly (ART)
		Survey data (self-report)	0, 6, and 12 months
	Proportion of days covered (# of dispensed days of medication/# of days between refills)	Intake and Record extraction	Weekly (ART)
Prevention (transmission risk)	Number of unprotected sex acts by partner HIV status	Survey data (self-report)	0, 6, and 12 months

Because the volume and intensity of the intervention might vary, particularly in the PN arm, we will also capture intervention exposure or dosage as a secondary exposure measure. Dose (minutes) of intervention received will be used for per protocol analyses. In the PN arm, this will include recording client data on frequency and duration of in-person meetings and phone communications with the navigator. Delivery and response to SMS messages for both intervention arms will be recorded with a standard duration of exposure (for example, 30 seconds) for each message, including two-way messaging. Any phone or in-person follow-up to SMS messages will be recorded separately. Secondary outcomes include linkage to HIV care, adherence to medications, and transmission risk behavior, as described in Table 1.

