In South Africa, the government continues to sponsor national HIV testing campaigns and has expanded ART eligibility, first to those with a CD4+ cell count of 350 cells/μL or less and recently to those with a CD4+ cell count of 500 cells/μL or less [12, 13]. Although treatment expansion is critical, current losses along the HIV care cascade are impeding HIV prevention gains. National data from 2012 indicated that 65 % of the population had been tested for HIV; however, only 37.8 % of HIV-positive men and 55 % of HIV positive women were aware of their HIV status [7]. Additionally, once diagnosed, many do not initiate care or treatment. A study in Cape Town found that only 62.5 % of recently diagnosed patients received a CD4+ test result within 6 months; 66.7 % of those that were eligible for ART initiated treatment; and only 46.3 % of those not ART eligible returned for a subsequent CD4+ test [14]. In a study in rural Kwa-Zulu Natal, only 44.9 % of the HIV-positive patients not yet ART eligible returned for subsequent CD4+ tests within 13 months [15]. To summarize, whereas South Africa has the largest antiretroviral program in the world [16], only 52 % of patients eligible for ART are estimated to currently receive treatment [17]. These failures to engage patients in care are exacerbated by further considering loss to follow-up after ART initiation, which has long-lasting implications, worsening outcomes for PLHIV, even if they return to care [18].

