### Participant eligibility and recruitment

We will be enrolling 750 participants, with a target of 42 (range = 30-55) participants at each facility. All participants must be diagnosed with HIV within 1 year preceding their enrollment. Participants must also be 18 years or older, have access to a cellular telephone where they are willing to receive automated text messages with HIV-related content, and be willing and able to give informed consent (not under the influence of illicit substances, or seemingly emotionally unstable at the time of recruitment and enrollment). Written informed consent will be obtained from all participants prior to enrollment in the study.

We aim to recruit an equivalent number of men and women and ensure that the sample has substantial representation (minimum of 30 %) of clients who do not yet quality for ART in order to assess the linkage and retention for both clients who initiate ART and those who do not. To accomplish this balance, recruitment will be completed using two strategies. The first strategy includes recruiting clients who present at the clinic for HIV testing and receive a positive diagnosis for the first time, or those who are returning to collect their initial CD4+ test results. Recruitment will be systematic: all of those presenting for an HIV test or for an initial CD4+ test result will be approached by clinic staff about their interest in participating in the study. We initially estimated that between 50 % and 60 % of those recruited during HIV testing would have an ART-qualifying CD4+ cell count at the time of recruitment [38]. Because the national guidelines have recently changed to increase qualifying CD4+ to 500 or less, it is more likely that 70 to 80 % of the individuals newly diagnosed after January 2015 will qualify for ART.

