### Sample size estimation

We aim to enroll 750 patients across the 18 participating clinics, with the goal of ensuring that each of the 18 clinics has at least 30 participants, and no site more than 55 to guarantee a well-balanced sample and minimize variability. We anticipate that approximately 20 % of the sample will discontinue study participation, largely due to extensive migration in the area. This estimate of attrition is grounded in on our pilot experience, during which 10 % of participants moved out of the area during a 3-month observation period. We therefore anticipate an evaluable sample of 600 participants over 1 year. Under the assumption that only 50 % of participants in the SOC clinics will remain in care [10, 38], this sample size will provide 80 % power to observe a 20 % to 23 % difference in patient retention at 12 months between the PN and SOC or SMS and SOC arms and a 17 % to 20 % difference between the PN and SMS arms. These estimates assume a two-sided alpha of 0.05 and a coefficient of variation of 0.15 to 0.20 or an intra-cluster correlation of 0.0225 to 0.04 based on a review of the recent literature around sample size estimation in large cluster randomized trials [52, 53].

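### The primary retention outcome is defined only for participants who have started ART and for those not yet eligible, so eligible non-starters and never-staged participants have no stated value

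*Protocol article*

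**What the plan says.** The protocol article states the primary outcome twice under Measures, each time in two branches.

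- **ART branch.** The text defines retention "for patients on ART as the proportion of patients who have initiated ART who remain on treatment at 6 and 12 months". Table 1 has "Patients on or initiating ART who remain on treatment 6 and 12 months later (with documented receipt of treatment".
- **Pre-ART branch.** The text has "for patients who are not yet eligible as the proportion of patients who undergo a repeat CD4 test at 6 months and 12 months", timed from the initial CD4. Table 1 has "Patients not ART eligible who have a repeat CD4 test at 6 months and 12 months after initial CD4".

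CD4 staging within 3 months of diagnosis, and ART start within 3 months of staging among eligible participants, appear only as secondary linkage outcomes.

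Other sections imply a wider population. Participant eligibility and recruitment wants enough pre-ART clients "to assess the linkage and retention for both clients who initiate ART and those who do not". Analysis makes the primary analysis intention-to-treat. Sample size estimation assumes that 50 % of participants in control clinics remain in care and says "We therefore anticipate an evaluable sample of 600 participants over 1 year". The Abstract times the primary outcome at 12 months after enrolment.

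**The concern.** The two branches do not cover everyone enrolled. About 75 % of participants are to be recruited at a first positive test or when collecting the initial CD4 result. For them ART start, and often staging, comes after enrolment in a clinic whose arm is already fixed. Those who turn out to be eligible but never start fit neither branch, and those never staged cannot be placed in one.

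Both interventions aim to improve linkage to care and treatment. A denominator of starters therefore depends on something the interventions are meant to change. An arm that brings more hesitant patients onto ART adds harder-to-retain people to its own denominator and may look worse for doing so. The same outcome feeds the cost per person retained, so the ambiguity carries into the economic analysis.

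**Working it through.** **1. The plan's power figures reproduce.** Cluster size is m = 600/18 = 33.3, the base rate is 50 %, and alpha is 0.05 two-sided. The ICC is CV² × p/(1 − p) at p = 0.5, which gives 0.0225 for CV 0.15 and 0.04 for CV 0.20. The design effect 1 + (m − 1) × ICC is 1.7275 and 2.293.

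| Comparison at 80 % power | ICC 0.0225 | ICC 0.04 | Plan |
|---|---|---|---|
| Intervention (7 clinics) v control (4) | 19.4 points | 22.1 points | 20 to 23 |
| PN (7) v SMS (7) | 16.7 points | 19.2 points | 17 to 20 |

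The plan's figures are these rounded up, so the sample-size arithmetic is not in question.

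**2. How many eligible non-starters?** Recruits by the first strategy: 0.75 × 750 = 562.5. The protocol expects 70 to 80 % of people diagnosed after January 2015 to qualify for ART (earlier estimate 50 to 60 %). The Background cites a study in which "66.7 % of those that were eligible for ART initiated treatment", so 33.3 % did not. Using that rate here is an assumption. All recruits are taken as staged, and recruits from registers are left out.

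- Same start rate in every arm, 70 to 80 % eligible: 562.5 × 0.70 × 0.333 = 131 and 562.5 × 0.80 × 0.333 = 150, or 17 to 20 % of 750.
- Same start rate, 50 to 60 % eligible: 94 to 112, or 12.5 to 15 %.
- Start of 85 % (assumed) in the 14 intervention clinics and 66.7 % in the 4 control clinics, 70 to 80 % eligible, enrolment in proportion to clinics: 562.5 × (4/18 × 0.333 + 14/18 × 0.15) × 0.70 to 0.80 = 75 to 86, or 10 to 11 %.

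**3. Effect on power if they were left out.** In the first case the evaluable number falls from 600 to about 480 to 495. Power against control falls from 82.5 % to about 77 to 78 % (20-point difference, ICC 0.0225), and from 83.2 % to about 79 to 80 % (23 points, ICC 0.04). The loss is small.

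**4. Can the direction change?** All inputs here are assumptions except the 66.7 %, which comes from the background study. ART start is 66.7 % in control and 85 % under intervention. Retention is 80 % in those who would start anyway and 50 % in the extra 18.3 %. Non-starters count as not retained.

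- Starters only: control 80.0 %; intervention (0.667 × 0.80 + 0.183 × 0.50)/0.85 = 73.5 %. Difference −6.5 points.
- All eligible: control 0.667 × 0.80 = 53.4 %; intervention 0.534 + 0.0915 = 62.5 %. Difference +9.1 points.
- With extra-starter retention of 40 to 70 %: −8.6 to −2.2 points in starters, +7.3 to +12.8 in all eligible.

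If a fraction v of non-starters in both arms were instead scored as retained because they attend care, the all-eligible difference would be 0.183 × (0.50 − v). It stays positive while v is below 50 %.

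**The case against.** The strongest reply is that the article never says these participants are excluded. Its intention-to-treat statement, its aim to study clients who do not initiate, and its all-participant control rate all suggest that everyone was meant to count. A full protocol or analysis plan, not shown, could say how they are scored. This stands as a limit: exclusion is the literal reading, not stated text. It does not remove the point, because the article gives the denominators explicitly, twice, and they conflict with its other sections.

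A reader might infer more than the documents support:

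- **That about 40 % of participants lack a value.** The Background reports that "only 62.5 % of recently diagnosed patients received a CD4+ test result within 6 months", and adding the remaining 37.5 % as never staged gives 39 to 41 %. But receipt of a result is not staging; Table 1 lists the two separately. Some recruits are already collecting a result when they enrol.
- **That every non-starter is a care failure.** Someone eligible who attends visits without ART is arguably retained in care.
- **That the trial will show the wrong sign.** The reversal rests on assumed inputs and covers eligible participants only. The pre-ART branch (at least 30 % of the sample intended) and register recruits would dilute it.
- **That the 600 is wrong.** It is 750 less 20 % attrition.

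Imputation is not an answer. The plan imputes missing values under a missing-at-random assumption, but whether someone never treated remained on treatment is not an unobserved value of a defined outcome.

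**Conclusion.** The concern holds as a fault in the stated definition of the primary outcome. Taken literally, Measures and Table 1 give no value to eligible non-starters or never-staged participants and make the denominator depend on post-randomisation events that the interventions target. That conflicts with Analysis, with Participant eligibility and recruitment, and with Sample size estimation.

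The eligible non-starters alone could be roughly 10 to 20 % of those enrolled, depending on eligibility and on whether the interventions raise ART start. This rests on one background study's initiation rate. The number never staged cannot be derived from the document. The loss of power would be modest. The more serious risk is that conditioning on ART start can change the direction of the comparison, which the illustration shows to be possible, not expected. The definition should be settled before outcomes are compared by arm; otherwise the denominator could be chosen with results in view.

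**What to change.** Reword Measures and Table 1 so that the primary GEE uses all enrolled participants as the denominator, each with one prespecified binary retention value at 12 months after enrolment.

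- Eligible non-starters and never-staged participants stay in the denominator. They count as not retained unless a prespecified qualifying HIV-care visit near 12 months is documented.
- As a sensitivity analysis, apply a stricter version in which no documented ART counts as not retained.
- State how participants whose eligibility changes during follow-up are scored, so that becoming eligible late while attending care is not counted as failure.
- Report the proportion of starters remaining on treatment as a descriptive cascade figure only.

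The cost is lower absolute retention percentages and a little more wording. No new data collection is needed: Data collection procedures already provides for extraction of visits, medications and CD4 results for participants on and off ART.

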Given the promise of these intervention options, we designed a cluster randomized trial to assess the efficacy of an SMS intervention and a peer navigation intervention to improve retention in care, timely linkage to care and treatment, ART adherence, and prevention behaviors in South African primary health clinics in the North West Province.

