### Analysis

Our preliminary analysis will include presentation of participant demographic characteristics, service usage, acceptability of intervention approaches and self-reported sexual behavior within each of the three study arms using descriptive statistics (one-way and cross-tabular frequency tables and, for continuous variables, measures of central tendency). Measures of variability will account for repeated measures (multiple patients) and consequent correlation of variables (clustering) within each health facility. We will employ multiple imputation (MI) using chained equations to account for missing data. This procedure assumes that incomplete data arise from a missing-at-random (MAR) process, under which missingness is random conditional on observed covariables and observed outcomes rather than a missing-completely-at-random (MCAR) mechanism [43], thus making fewer assumptions about the nature of the missing data. We will conduct sensitivity analysis using weighted MI to evaluate the robustness of the MAR assumption [44].

Our primary analyses will employ an intention-to-treat (ITT) approach. We will employ logistic generalized estimating equations (GEE) to compare patient retention between intervention arms. We will also evaluate secondary outcomes (linkage, adherence and prevention behaviors) using an ITT analysis, as described above. We will employ GEE rather than mixed effects models as this approach allows us to estimate the effect of the intervention at the level of the population, rather than at the level of the individual. As our interventions will be implemented at the level of the health system, it is important to estimate the effect of the intervention at the level it is implemented [45]. Further, previous research has suggested that adjustment for confounding can improve the efficiency of estimates in the context of randomized trials [46]. We will thus conduct sensitivity analyses employing causal inference methods to account for any imbalance in distribution of site- and individual-level co-variables across study clinics. We will employ targeted maximum likelihood estimation [47], which allows estimation of both site- and individual-level co-variables, to minimize bias and improve efficiency of estimates of effect in the context of small sample sizes [48].

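### Primary retention is defined only for ART starters and not-yet-eligible patients, so eligible participants who never start ART have no primary outcome and the denominator depends on a post-randomisation event

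*Protocol article*

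**What the plan says.** The Measures section of the Protocol article builds the primary outcome from two groups, in these words: "proportion of patients who have initiated ART who remain on treatment at 6 and 12 months and for patients who are not yet eligible". For the second group the measure is a repeat CD4 test at 6 and 12 months. Table 1 repeats the split. Its first row is "Patients on or initiating ART who remain on treatment 6 and 12 months later (with documented receipt of treatment", and its second is "Patients not ART eligible who have a repeat CD4 test at 6 months and 12 months after initial CD4".

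Four other statements bear on this:

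- **Starting ART is a separate outcome.** Under linkage, Measures also tracks "whether eligible participants receive ART within 3 months of CD4 staging". The end of the Background says the interventions are meant to "improve retention in care, timely linkage to care and treatment, ART adherence, and prevention behaviors".
- **Analysis principle.** The Analysis section states: "Our primary analyses will employ an intention-to-treat (ITT) approach".
- **Planning rate.** Sample size estimation assumes that 50% "of participants in the SOC clinics will remain in care". It takes 600 of 750 as evaluable, reduced only for 20% discontinuation.
- **Recruitment.** Participant eligibility and recruitment plans 75% of the sample from people at HIV testing or a first CD4 result, and 25% from clinic registers. It treats pre-ART patients as those not yet eligible for ART.

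**The concern.** An eligible participant who never starts ART has not initiated ART and is not awaiting eligibility. Neither group holds that person, so the primary outcome has no value for them. This is one of the losses along the care cascade that the trial was set up to reduce.

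For most participants, starting ART comes after the clinic was randomised and after enrolment, and the interventions are designed to raise it. Entry to the ART denominator can therefore be affected by treatment. If an intervention brings hesitant patients onto ART and they are harder to keep there, they enter its denominator, while their counterparts in standard-of-care clinics are not counted at all. The retention comparison is then between differently selected groups, and success on a secondary outcome can count against the primary one. The cost per person retained would inherit the same problem.

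**Working it through.** **1. The plan's own power figure.** Clinic size m = 600/18 = 33.3. Design effect = 1 + (m − 1) × ICC, which is 1.73 at ICC 0.0225 and 2.29 at 0.04. With variance 0.25 in each arm, detectable difference = (1.96 + 0.84) × √(0.25/n₀ + 0.25/n₁), where n₀ and n₁ are clinics × m / design effect.

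| Comparison | ICC 0.0225 | ICC 0.04 | Stated |
|---|---|---|---|
| 4 v 7 clinics (against standard of care) | 20.0 points | 23.0 points | 20-23 |
| 7 v 7 clinics (peer navigation v SMS) | 17.0 points | 19.6 points | 17-20 |

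The figures reproduce with all 600 evaluable participants in the denominator.

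**2. How many could be left out.** Inputs from the article:

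- 75% recruited at testing or first CD4 result, and 25% from registers
- 50-60% ART-eligible among the former (the initial estimate)
- about 90% eligible among register recruits
- at least 30% of the sample not yet qualifying
- a cited Cape Town study in which 66.7% "of those that were eligible for ART initiated treatment", so 33.3% did not

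Share with no outcome = 0.75 × eligible share × 0.333.

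- At 50%: 0.75 × 0.50 × 0.333 = 12.5%, or 94 of 750.
- At 60%: 0.75 × 0.60 × 0.333 = 15.0%, or 112 of 750.
- At the highest share the 30% minimum allows: (0.70 − 0.25 × 0.90)/0.75 = 63.3%. Then 0.75 × 0.633 × 0.333 = 15.8%, or 119 of 750.

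Some eligible register recruits may also not have started. If the same third applied to all of them, they would add 0.25 × 0.90 × 0.333 = 7.5% (56 of 750). That is an upper bound, because many will already be on ART.

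**3. What it can do to the estimate.** Let E be the eligible share, i the share of those who start, r retention among starters and q the repeat-CD4 share among the not eligible.

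- Over all enrolled: E·i·r + (1 − E)·q
- As defined: the same numerator divided by E·i + (1 − E)

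Inputs from the article: E = 0.70 (the most the 30% minimum allows), q = 0.463 and standard-of-care i = 0.667, the last two from the cited study. Assumed: r = 0.75, intervention i = 0.85, and no effect on anyone who would have started anyway. For simplicity i applies to all eligible participants, including register recruits.

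Standard of care: 0.70 × 0.667 × 0.75 + 0.30 × 0.463 = 0.489 over all enrolled, close to the planned 50%. As defined it is 0.489/0.767 = 0.638.

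Intervention: numerator = 0.489 + 0.70 × (0.85 − 0.667) × retention of extra starters; denominator as defined = 0.70 × 0.85 + 0.30 = 0.895.

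| Retention of extra starters (assumed) | All enrolled, difference | As defined, difference |
|---|---|---|
| 30% | 0.528 − 0.489 = +3.8 points | 0.589 − 0.638 = −4.8 points |
| 50% | 0.553 − 0.489 = +6.4 points | 0.618 − 0.638 = −2.0 points |
| 75% | 0.585 − 0.489 = +9.6 points | 0.654 − 0.638 = +1.6 points |

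Under these assumptions the sign reverses only when extra starters are retained at less than 63.8%. If initiation is unchanged and nothing else differs, both differences are zero. A benefit among those who would start anyway works against the reversal: in the 50% row, about 4 points of extra retention in that group (0.0197 × 0.895/0.467) brings the difference as defined back to zero.

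**4. Effect on power.** With unpooled variance, the detectable difference against standard of care is 19.4-22.2 points at 600 evaluable. It is 20.3-22.9 at 510 (15% excluded) and 20.6-23.2 at 486 (19% excluded). The loss is about 1 point, so power is not the main issue.

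**The case against.** The strongest reply is that the exclusion is inferred. No sentence says that eligible non-starters leave the analysis. Measures and Table 1 may only describe how retention is ascertained by ART status, while the ITT statement and the 600 evaluable participants point to everyone being analysed. An article may leave the combination of the two groups into one variable to a fuller document. It is fair that the plan does not explicitly drop these people. But the rule it does state, in both text and table, gives them no value. ITT fixes the arm in which a person is counted, not what counts as success. Multiple imputation deals with missing values, not undefined ones, and the targeted maximum likelihood sensitivity analysis addresses covariate imbalance.

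A second reply is that non-initiation remains visible, since ART start within 3 months is analysed separately by arm. That helps interpretation but does not repair the primary comparison.

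Three stronger readings are tempting, and the article does not support them:

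- **That 17.5-20% of participants are affected.** This uses 70-80% eligibility, which the article gives only for diagnoses after January 2015. It also breaches the 30% minimum: with the register recruits, not-yet-qualifying participants would be 25% and 17.5%. Recruitment began in October 2014.
- **That the result will be biased towards the null or reversed.** This depends on assumed rates. The 66.7% is from one outside study and is not a 12-month rate for consented trial participants.
- **That the whole ART denominator is selected by the intervention.** Register recruits already on ART started before they were individually exposed, so the conditioning applies mainly to the 75%.

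**Conclusion.** The point stands as a defect in the stated primary outcome. Eligible participants who never start ART have no primary-outcome value. If the definition is followed, the comparison conditions on a post-randomisation event that the interventions target, and it departs from both the ITT statement and the all-participant 50% planning rate. Participants never CD4-staged, and those who move from not eligible to eligible during follow-up, are not clearly assigned either.

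The plausible extent is about 12.5-16% of participants (94-119 of 750), with some register recruits possibly adding to it. This rests on borrowing the cited 66.7%. The direction and size of any bias cannot be settled from the article. Attenuation and, in some scenarios, sign reversal are possibilities, not predictions. Because the definition decides who enters the primary comparison, it should be corrected before outcomes are analysed.

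**What to change.** Define one binary 12-month retention outcome for every enrolled participant:

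- **Retained:** documented ART receipt at 12 months or, if still not ART-eligible, the repeat CD4 test.
- **Not retained:** among others, participants known to be eligible who have not started ART by 12 months.
- **Stated rule:** say which outcome applies to participants never CD4-staged and to those who change from not eligible to eligible.
- **Unobserved:** outcomes that are truly unknown, for example after moving away or withdrawal, stay under the planned multiple imputation. Scoring everyone else as a failure would override that plan for the 20% expected to discontinue.

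Report retention among starters as secondary or descriptive.

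The cost is modest. The data fall within the planned record extraction, and with all 600 evaluable participants in the denominator the stated 20-23 and 17-20 point detectable differences still apply. Absolute retention figures will be lower. The primary outcome of a registered trial already recruiting must be formally amended, and this must be done before outcome analysis. Counting an eligible patient who attends care without ART as not retained is a choice of definition and should be stated as such.
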